### Intervention

On the basis of our previous research [25], participants assigned to the acupuncture group will receive acupuncture stimulation, exercise and cognitive training. Acupuncture will be performed by a senior acupuncturist. The fixed acupoints are EX-HN1 (Sishencong) and GV20 (Baihui). The adhesive pads will be pasted on the acupoint surface after skin disinfection. The acupuncture needles will be inserted through the adhesive pads approximately 1 cm into the skin and left in place for 30 min, performing small thrusts and rotations every 10 min.

Participants assigned to the control group will receive sham acupuncture stimulation, exercise and cognitive training. The sham acupoints (1 cm away from the acupoint) used for the control group are separate from conventional acupoints or meridians. The adhesive pads will be pasted on the sham acupoint surface, placebo needles with a blunt tip replacing traditional needles will be inserted through the adhesive pads without penetrating the skin, and no manipulation will be performed. The treatment course will be three times a week for 12 weeks.

The exercise and cognitive training measures, based on our previous research [25], will be analogous to those of the control group. Exercise training will include Tai Chi, square dance, ball games, aerobic gymnastics, jogging, and other aerobic exercises acceptable to patients (5 times a week for 12 weeks, 1 h/time). The first three cognitive training sessions will be performed by professional rehabilitation doctors and rehabilitation therapists, during which family members will be trained. The subsequent training will be completed by family members at home. At the 4th and 8th weeks, the rehabilitation doctors will decide whether to adjust the training program after assessment.

### Randomization

Participants will be randomly divided into treatment (active acupuncture + exercise/cognitive training) and control groups (sham acupuncture + exercise/cognitive function training) using the method of a random parallel controlled trial as in our previous research [25]. Qualified subjects will be numbered and grouped by the random grouping numbers generated by SPSS software to ensure balance between the two groups.

### Blinding

We will try to ensure that participants receive comparable treatment measures. All researchers and statisticians responsible for data recording will be blind to the randomization, as in our previous research [25].

### Clinical assessment

The patients will be examined and MCI will be diagnosed by a trained neurologist. Clinical information will be collected through patient interviews and a review of medical records and will include the following: age of MCI onset; history of MCI; onset type; number of episodes; and MMSE, Montreal Cognitive Assessment, and Functional Activity Questionnaire scores. We will also collect detailed information on defecation status, number of completely autonomous bowel movements per day, and stool characteristics (Bristol Stool Form Scale). Data on patients’ diets will be collected with the Food Frequency Questionnaire [28, 29]. The mental state and behaviour of patients with MCI will be evaluated. The GDS will be used to screen depression [30].

### Outcome measurements

Scales of clinical dementia rating (CDR, MMSE, MoCA) and ADL will be collected at baseline, during the treatment (weeks 4 and 8), at the end of the treatment, and at months 4 and 6 after the intervention.

#### Primary outcome

According to the research objectives, the improvement of cognitive function as assessed by MoCA will be regarded as the main result of the study. The MoCA covers a wide range of cognitive fields, including attention and concentration, executive function, memory, language, visuospatial structure skills, abstract thinking, calculation, and orientation. It is specifically designed to screen for MCI with high sensitivity (80–100%) and purposefulness (50–76%) [31]. The patient’s faeces will be stored in the refrigerator at − 80 °C. 16 S rDNA sequencing will be used to detect the changes in intestinal flora distribution in patients.

#### Secondary outcomes

Secondary measures will include the MMSE and Functional Activity Questionnaire (FAQ) scores. The MMSE has 11 questions and tests five aspects of cognitive function. The highest score is 30 points, and a score of < 24 points is regarded as abnormal dementia [32]. Daily abilities include basic activities of daily living (BADL) and instrumental activities of daily living (IADL). The former refers to the most basic abilities required for independent living, and the latter refers to complex daily or social activities. The diagnosis of MCI requires normal BADL and slight impairment of IADL. FAQ is a commonly used IADL evaluation scale that has been proven to distinguish between people with normal cognitive function and those with MCI (level II evidence) (Professional Committee of cognitive disorders, Chinese Medical Association, 2018 Chinese guidelines for diagnosis and treatment of dementia and cognitive impairment (V): diagnosis and treatment of mild cognitive impairment 2018) and can be used as an indicator of the transformation from MCI to AD (level II evidence) [33].

### Blood sampling and assay

Within a restricted time window (08:00–10:00), venous blood samples will be collected from participants in the fasting state. Genomic DNA will be extracted from leukocytes using a commercial kit (Wizard Genomic DNA Purification Kit; Promega, Madison, WI, USA; product no. A1120), and the V3/V4 hypervariable region of the *16 S* gene will be amplified by PCR using primers rs429358-rs7412-F1 (TCGGAACTGGAACAACT) and rs429358-rs7412-R1 (ACCTGCTCCTTCACCTCGT). The reaction will contain 1 µl each of forward and reverse primers (10 µmol/l), 25 µl of 2× EasyTaq PCR SuperMix, 2 µl DNA, and 21 µl ddH_2_O. The expected PCR product is 482 bp and will be resolved by agarose electrophoresis before confirmation by sequencing (Hangzhou Meredith Biotechnology Co., Hangzhou, China) on an ABI3730xl system (Applied Biosystems, Foster City, CA, USA) [34].

### Faecal microbiome analysis

The V3/V4 sequence will be analysed by a bioinformatics approach with an error correction protocol. Quality filtering, including pruning low-quality bases at the beginning and end of each read (https://github.com/najoshi/sickle), will be performed before assembling paired reads using Paired-End reAd mergeR v0.9.1 (http://www.exelixis-lab.org/web/software/pear), with Bayes Hammer used for error correction [35, 36]. The size selection filter and Basic Local Alignment Search Tool (BLAST: https://blast.ncbi.nlm.nih.gov/Blast.cgi) search will be set to the expected amplifier size.

Quantitative Insights Into Microbial Ecology 2 (http://qiime.sourceforge.net/) will be used to analyse corrected and assembled reads [30, 37]. De novo ultrafast sequence analysis and open reference operational taxonomic unit (OTU) clustering will be performed, and de novo chimaera detection will be conducted using UCHIME v5.1 (http://drive5.com/uchime) [38, 39]. Taxonomic classification of OTUs will be conducted using naive Bayesian RDP Release v11.5 (Ribosomal Database Project; http://rdp.cme.msu.edu/) and the Green genes classification taxonomic database (https://greengenes.secondgenome.com/).

The Bray–Curtis distance, which is based on count statistics of sortable OTUs [40], will be used to determine differences in β diversity, and principal coordinate analysis will be used for 3-dimensional visualization of the distance matrix. The significance of diversity differences between groups will be evaluated with the Adonis test, with a test level of α = 0.05.

Genus-level differences in faecal microbiota between MCI patients with and without the *ApoE* ε4 allele will be determined based on linear discriminant analysis (LDA) effect size (log linear LDA score > 2.0 and P value < 0.01).

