## Methods

### Study design and population

This single-centre, randomized, assessor- and data analyst-blind controlled study will include 2 groups of patients—those with and without *ApoE ε4* gene polymorphism (n = 60/group)—recruited from the outpatient department of Zhejiang Hospital. Each group of patients will be randomly assigned to the acupuncture group or the sham acupuncture group. The study protocol was approved by the Ethics Committee of Zhejiang Hospital (2021-LS-12 K) on January 25, 2021. Each participant and/or their guardian will be informed of the nature of the study by telephone and will be required to sign the informed consent form before enrolment, which will take place from March 2021 to December 2022. Data will be analysed, and the results will be published in 2023. The proposal is depicted in Fig. 1.

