## Discussion

MCI is the prophase state of dementia and the key phase for early intervention. At present, there is no drug that can be used in the MCI stage. Acupuncture reflects the value of early intervention in MCI. The purpose of this study is to evaluate the difference in the curative effect of acupuncture on MCI patients with and without the *ApoE ε4* gene polymorphism and to explore the relationship between the acupuncture mechanism and changes in the intestinal flora. We hope to be able to provide assessable biomarkers associated with acupuncture treatment.

*ApoE* ε4 is associated with degeneration of brain capillary pericytes that maintain blood–brain barrier (BBB) integrity [8, 41]. *ApoE* ε4 carriers (ε3/ε4 or ε4/ε4 alleles) are distinguished from noncarriers (ε3/ε3) by BBB breakdown in the hippocampus and medial temporal lobe [8]. Disruption of the gut flora balance in pathogen-free mice has been linked to increased BBB permeability in the embryonic stage of development and in adults [42] as well as central nervous system abnormalities such as cortical myelination, hippocampal neurogenesis, cognitive function, and memory formation [43]. It has been suggested that systemic inflammation induced by compounds secreted by bacteria impairs the BBB and promotes neurodegeneration [44–46]. We hypothesize that specific types of microbiota contribute to *ApoE* ε4-associated breakdown of the BBB in patients with MCI and can serve as biomarkers for progression to AD.

EX-HN1 (Sishencong) and GV20 (Baihui) have the local effect of regulating brain function. Acupoints can regulate the brain network by increasing connections between cognitive-related regions, thereby improving cognitive function in MCI patients [47]. By improving brain function, acupoints further affect the movement, sensation, and secretion of the gastrointestinal tract through the descending pathway of the gut–brain axis and regulate the composition and behaviour of the gut microbiota [48]. The purpose of our research is to elucidate the relationship between acupoints and gut microbiota.

Clinically, acupuncturists treat patients individually based on their symptoms. As the fixed acupuncture program can reduce research deviation and is more conducive to promotion, we selected fixed acupoints.

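### The rule for declaring genera that differ by ApoE ε4 status uses P < 0.01 per genus with no correction across genera, so some named genera may be chance findings

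*Protocol article*

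**What the plan says.** Under Faecal microbiome analysis, the protocol article fixes both the contrast and the decision rule. The contrast is "Genus-level differences in faecal microbiota between MCI patients with and without the" ε4 allele. The differences "will be determined based on linear discriminant analysis (LDA) effect size", and the cut-offs are given in brackets: "effect size (log linear LDA score > 2.0 and P value < 0.01". No correction across genera is named there.

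The only multiplicity rule in the article is the last sentence of Data analysis. It assigns Bonferroni to pairwise comparisons when there are several groups. The carrier contrast has two groups and many genera, so that sentence does not reach it.

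Under Study design and population there are 60 patients in each genotype group, and randomisation takes place within genotype: "Each group of patients will be randomly assigned to the acupuncture group or the sham acupuncture group". Under Primary outcome, sequencing of the flora is described next to the MoCA. The Discussion puts forward the hypothesis that particular microbiota contribute to ε4-related breakdown of the blood-brain barrier and could act as biomarkers of progression to AD.

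**The concern.** Method, effect-size cut-off and P cut-off are all stated, so an analyst could apply the rule as printed and name genera from it. Each genus has its own 1% chance of a false P value, and these chances add up over all genera examined. The LDA score measures how large a difference looks in the sample. It removes small chance differences and lets large ones through, and it does not hold any family-wise or false discovery rate at a chosen level.

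At stake is the credibility of the list of genera. The article looks to specific microbiota as possible markers of progression, and this is the one stated analysis that would name genera by ε4 status. A chance genus on that list could be taken forward as a candidate.

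**Working it through.** **The plan's own figure.** The article states no error rate for the genus analysis and no number of genera, so there is no figure to reproduce.

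**Inputs from the article.** Per-genus level 0.01; LDA score above 2.0; 60 carriers and 60 noncarriers.

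**Assumptions.** Number of genera m = 50, 100, 200 or 300. Complete null (no genus truly differs). Independent tests for the closed formulas.

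**Step 1: the P value condition alone.** Expected false genera = m × 0.01. Chance of at least one = 1 − 0.99^m. Bonferroni level for comparison = 0.05/m.

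| m | Expected false genera | Chance of at least one | 0.05/m |
|---|---|---|---|
| 50 | 0.5 | 39% | 0.001 |
| 100 | 1.0 | 63% | 0.0005 |
| 200 | 2.0 | 87% | 0.00025 |
| 300 | 3.0 | 95% | 0.00017 |

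The chance of at least one passes 50% at ln(0.5)/ln(0.99) ≈ 69 genera.

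**Step 2: both conditions together.** The stated rule also requires LDA > 2.0, so Step 1 overstates it. A rough null simulation used 300 trials per setting, 60 v 60 patients, correlated compositional counts and rank-sum tests. The LDA score was approximated from the difference in mean relative abundance.

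| m | False genera, P < 0.01 only | False genera, P < 0.01 and LDA > 2 | At least one, both conditions | At least one, Benjamini-Hochberg at 5% |
|---|---|---|---|---|
| 50 | 0.56 | 0.49 | 29% | 7% |
| 100 | 1.00 | 0.72 | 45% | 6% |
| 200 | 1.78 | 1.12 | 58% | 1% |

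The second column agrees roughly with m × 0.01, which supports the set-up. The simulation error of the 45% is √(0.45 × 0.55/300) ≈ 0.03. For the Benjamini-Hochberg 7% it is √(0.07 × 0.93/300) ≈ 0.015, so 7% and 6% are compatible with the nominal 5%.

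**Step 3: reading the two steps together.** The LDA cut-off lowers the number of false genera, but the chance of at least one still rises with m. With both conditions, the expected number of false genera is below one at 50 and at 100 genera, and passes one somewhere between 100 and 200.

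**The case against.** **The LDA filter and the unknown genus count.** The 63% to 95% range ignores half of the stated rule and rests on an assumed m. This stands as a limit on size: it would be too strong to say that false genera are to be expected whatever the genus count. It does not remove the point, because 29% to 58% with the filter is still far above 5%.

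**A condensed article.** The text says only P value, so the absence of a correction is inferred, and a fuller plan may add one. That is possible. Still, the article prints specific cut-offs as the rule, and those would then need to be brought into line.

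**A pilot.** The limitations describe a single-centre pilot, which favours reading the genus analysis as screening. This softens the point, but the flora measure appears under Primary outcome and the Discussion speaks of biomarkers.

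**Confounding.** A reader might infer that the carrier difference is confounded, since genotype is not randomised, "diets will be collected with the Food Frequency Questionnaire" and stool data are recorded ("We will also collect detailed information on defecation status"), yet no stated microbiome analysis uses them. The documents do not support that. Nothing shows that diet or stool form differs by genotype. Genotype precedes both, so they may be mediators or precision variables, and stool form may be a consequence of the flora. The eligibility criteria already exclude recent antibiotics and probiotics and several bowel conditions. A covariate list is also something an article may leave to the analysis plan.

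**Wider use of the rule.** A reader might infer that the error multiplies over several contrasts, or that it undermines the hope expressed in "We hope to be able to provide assessable biomarkers associated with acupuncture treatment". The rule is stated for one contrast only, carriers v noncarriers, and that sentence concerns treatment. The relevant Discussion passage is the ε4 hypothesis.

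**Conclusion.** The point holds as a multiplicity defect in one stated rule. Followed as printed, it tests every genus at 0.01, and neither the LDA cut-off nor the Bonferroni sentence controls the error across genera. Under the complete null, the chance of naming at least one false genus is about 29% to 58% for 50 to 200 genera with both conditions. With the P value alone it is 39% to 95% for 50 to 300 genera.

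These figures depend on a genus count that the article does not give. The second range also assumes independent tests, and the first rests on an approximate LDA score and simulated abundances. If some genera truly differ, the expected number of false genera from the P value alone is 0.01 times the number that do not. The supported wording is that some named genera may be chance findings. That the carrier comparison is confounded is not shown.

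**What to change.** State that a genus is declared different between carriers and noncarriers only if its Benjamini-Hochberg q-value is below 0.05. Compute q-values over all genera tested in this contrast, including those that fall short of the LDA cut-off. Report the LDA score as a descriptive effect size.

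The cost is analysis wording and a shorter list. To declare k of m genera, the method needs the k-th smallest P value to be at most 0.05 × k/m. With 100 genera, a single declared genus needs P ≤ 0.05 × 1/100 = 0.0005 in place of 0.01. The new cut-off is stricter than 0.01 whenever fewer than 0.01/0.05 = one fifth of the genera are declared.

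Because genotype is not randomised, a carrier comparison adjusted for age, sex and the diet data already collected can be added as a sensitivity analysis only. It needs a defined summary of the diet questionnaire. Stool form is better left out of that adjustment, since conditioning on something downstream of the flora could remove part of the association under study.

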### Data analysis

Measurement data will be expressed as the means ± standard deviations, and count data will be expressed as frequencies. Data will be analysed using SPSS Statistics for Windows v21 (IBM, Armonk, NY, USA). Pearson’s χ2 test or Fisher’s exact test will be used to analyse classified variables. The t test will be used if the normal distribution and homogeneity test are satisfied, and the rank sum test will be used for nonnormality or nonuniformity of variance. The Kruskal‒Wallis test will be used for multigroup comparisons, and the Wilcoxon rank sum test will be used for comparisons between two samples. For repeated measurement data, repeated measurement analysis of variance will be used. For the pairwise comparison of multiple groups of data, the Bonferroni method will be used to adjust the test level.

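### The Data analysis section lets pre-tests pick the two-group test, sends unequal variances to the rank sum test, and does not say which named method gives the primary MoCA result

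*Protocol article*

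**What the plan says.** The primary clinical outcome is MoCA: "the improvement of cognitive function as assessed by MoCA will be regarded as the main result of the study" (Primary outcome). The Outcome measurements section has it recorded six times, the last two once the intervention is over: the scales "will be collected at baseline, during the treatment (weeks 4 and 8), at the end of the treatment, and at months 4 and 6". Allocation is made within ApoE groups: "Each group of patients will be randomly assigned to the acupuncture group or the sham acupuncture group" (Study design and population).

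The Data analysis section then gives rules for measurement data without tying any of them to an outcome:

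- Parametric branch: "The t test will be used if the normal distribution and homogeneity test are satisfied".
- Fallback: "the rank sum test will be used for nonnormality or nonuniformity of variance".
- Next sentence, with no condition attached. For several groups, a Kruskal–Wallis "test will be used for multigroup comparisons". For two groups: "the Wilcoxon rank sum test will be used for comparisons between two samples".
- Repeated data: "For repeated measurement data, repeated measurement analysis of variance will be used".

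Measurement data are summarised as means with standard deviations. No covariate or stratum term is named.

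**The concern.** Three things are fixed badly in the printed text.

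1. **The data choose the test.** The t test and the rank sum test address different hypotheses, so a pre-test result decides which question the p value answers.
2. **The fallback for unequal variance is wrong for a comparison of means.** The rank sum test takes its null distribution from two samples with one common distribution. If the means agree but the spreads differ, it need not hold its level. Welch's t test is built for that case.
3. **The primary MoCA analysis is not identified.** A t test, a rank sum test and a repeated-measures ANOVA can each claim the outcome. As named, none of them adjusts for baseline MoCA as a covariate or includes the ApoE stratum used in allocation.

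At stake are an undetermined primary p value, an error rate that drifts in some plausible situations, and lost precision in a trial of 120 people.

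**Working it through.** **The plan's own figure.** The Sample size estimation section plans a four-group one-way ANOVA with f = 0.4, α = 0.05 and power 0.9. With λ = N·f² = 96 × 0.16 = 15.36 and 3 and 92 degrees of freedom, power is 0.912. At N = 92 it is 0.898. So 96 reproduces as the smallest equal-group total. It does not settle which method decides MoCA.

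**Inputs.** Group sizes come from the protocol: 30 per cell, 60 per arm, and 96/2 = 48 per arm if 96 are evaluable. The protocol gives no MoCA SD, variance ratio or baseline–follow-up correlation, so these are assumed over ranges.

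**Step 1: how often chance picks the test.** Simulated normal data with SD 2.5 in both arms were rounded to whole points, 60 per arm, with Shapiro–Wilk in each arm and Levene's test, each at 0.05. The pre-tests are passed in 55% of trials. Type I error is not harmed: 5.9% for the two-stage rule and 5.9% for the t test, with simulation error √(0.05 × 0.95/4,000) ≈ 0.3 points. With SD ratio 2 and equal arms, the rule sends over 99% of trials to the rank sum test at 48 to 60 per arm, and 94% at 30 per arm.

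**Step 2: size of the rank sum test as a test of means.** Normal data, equal means, nominal 5%. Ranges are across repeat runs of 20,000 trials, simulation error about 0.15 points.

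| Group sizes | SD ratio | Rank sum |
|---|---|---|
| 30 v 30 | 1.5 | 5.2% |
| 60 v 60 | 1.5 | 5.5% |
| 30 v 30 | 2 | 5.5–5.8% |
| 60 v 60 | 2 | 5.5% |
| 30 v 30 | 3 | 6.9–7.0% |
| 22 v 30, smaller group more variable | 2 | 7.2–7.3% |
| 22 v 30, smaller group more variable | 3 | 8.5–8.6% |

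Welch's test stays at 4.7–5.1% where it was run alongside (30 v 30 and 22 v 30, SD ratios 2 and 3). Runs of 4,000 trials with whole-point scores and SD ratio 2 gave 5.1–5.3% for the rank sum test with equal arms. With 56 v 40 and the smaller arm more variable they gave 7.1% for the rank sum test, 7.0% for the two-stage rule and 4.4% for Welch. The size 22 comes from 30 × (1 − 0.25) = 22.5, the planned dropout falling wholly on one group.

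**Step 3: skewed data.** With gamma-distributed data (shape 2), equal means and SD ratios 1.5 and 2, the rank sum test rejects in 9.3% and 14.1% of trials at 30 per arm, and in 13.8% and 23.7% at 60 per arm. Welch rejects in 5.0–5.3%. The excess grows with sample size because the rank sum test is answering a different question.

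**Step 4: precision from baseline.** Let r be the baseline–follow-up correlation, with equal variances. Relative to follow-up variance 1, a change score has variance 2(1 − r) and ANCOVA has 1 − r². The ratio is (1 − r²)/[2(1 − r)] = (1 + r)/2, which is 0.75 at r = 0.5 and 0.90 at r = 0.8. For illustration, with a 0.5 SD difference and 48 per arm at r = 0.5, power is 0.69 for a change score and 0.81 for ANCOVA. At r = 0.7 it is 0.89 and 0.93.

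**The case against.** The strongest reply is that MoCA, measured at six visits, falls under the repeated-measures sentence, so the two-sample rules may never touch it. Baseline can then enter as a level of time, and the outcome is worded as improvement, which already implies comparison with baseline. The four groups are ApoE status by arm, so ApoE enters the multigroup and pairwise comparisons. A reader might infer that the plan ignores baseline MoCA and ApoE; for these reasons the text does not support that. What stands is narrower: the section does not say that repeated-measures ANOVA is the primary analysis, and it names no baseline covariate or ApoE term. The covariate detail alone could be left to a fuller document that is not shown.

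A reader might also infer that the conditional t-test rule and the Wilcoxon sentence flatly contradict each other. They need not. The second can be read as listing the rank tests on the nonparametric branch. The text does not say so, which makes it an ambiguity rather than a proven conflict.

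On size, the reply is largely right for equal arms and symmetric data. The 22 v 30 case needs all dropout in the more variable group; with the direction reversed the size is 4.3%. If acupuncture has no effect on anyone, the randomised arms share one distribution and the rank sum test keeps its level. The inflation concerns the weaker null of equal means with unequal spread. That is still the null that matters when results are reported as means, and unequal variance is the very condition under which the rule selects this test.

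**Conclusion.** The point holds in a limited form. The rule that unequal variance alone leads to the rank sum test is stated in the text and is not a valid remedy for a mean difference. The choice by pre-test and the unassigned primary MoCA method also stand.

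The error-rate cost is small with equal arms and symmetric data (at most about 5.8% at SD ratios up to 2). It is moderate at ratio 3 or with a smaller, more variable arm (about 7% to 8.6%), and larger if skew accompanies unequal spread. All of this rests on assumed SD ratios and shapes. Serious inflation of the MoCA result should not be inferred, because the protocol gives no SDs and the repeated-measures rule may govern MoCA.

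The gain from baseline adjustment is best stated against a change score, since the outcome is improvement: variance 0.75 to 0.90 of that comparison for an assumed correlation of 0.5 to 0.8. A larger gain against a bare follow-up comparison could be quoted, but the protocol does not state that it will use one.

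**What to change.** Before unblinded analysis:

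1. Name one primary MoCA analysis that is used whatever any normality or variance test shows. This would be a linear model (ANCOVA, or a repeated-measures model) at a stated time point, with arm, baseline MoCA and ApoE stratum, and robust standard errors. Report the adjusted mean difference with its 95% confidence interval.
2. Use Welch's t test in place of the rank sum test wherever unequal variance is the only concern.
3. State whether the Wilcoxon and Kruskal–Wallis sentence applies only to the nonparametric branch.

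The cost is analysis wording. Baseline MoCA and ApoE status are already scheduled to be collected, so no new measurement is needed. The Results section reports 98 participants at the time of writing, with final results still to come; it should not be assumed that data collection is complete.

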**Methods:**

This randomized assessor-blind controlled study will enrol MCI patients with and without the *ApoE* ε4 gene (n = 60/60). Sixty subjects with the *ApoE* ε4 gene and 60 subjects without the *ApoE* ε4 gene will be randomly allocated into treatment and control groups in a 1:1 ratio. Intestinal microbiome profiles will be evaluated by 16 S rRNA sequencing of faecal samples and compared between the groups.

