### Sample size estimation

Using GPower 3.1.9.6 to determine the sample size, a single-factor ANOVA was selected for prior analysis at the 4-group level, with a response size of 0.4, a test level of 0.05, a test efficacy of 0.9, a sample size of 96, and a 25% dropout rate. The final sample size was determined to be 120 people, with 30 people in each group, which was similar to that of other studies [20, 26, 27]. The necessary number of participants was recorded at baseline. Before the end of the enrolment period, more patients will be recruited to replace those who were excluded after baseline examinations.

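### One stated purpose is whether acupuncture's effect differs by ApoE ε4 status, but the plan fixes a single four-level group factor and states no arm-by-genotype term for MoCA

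*Protocol article*

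**What the plan says.** The Discussion states: "The purpose of this study is to evaluate the difference in the curative effect of acupuncture on MCI patients with and without" the ε4 polymorphism. The Study design section describes two genotype groups of 60 and says "Each group of patients will be randomly assigned to the acupuncture group or the sham acupuncture group"; the Abstract gives the ratio as 1:1. The Sample size section puts 30 people in each of four groups.

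For testing, the Sample size section says that "a single-factor ANOVA was selected for prior analysis at the 4-group level", "with a response size of 0.4". The Data analysis section names t or rank sum tests, then says that the Kruskal–Wallis "test will be used for multigroup comparisons, and the Wilcoxon rank sum test will be used for comparisons between two samples". It also says: "For the pairwise comparison of multiple groups of data, the Bonferroni method will be used to adjust the test level". Repeated-measures ANOVA is named for repeated measurements, without its factors.

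The main outcome is improvement in MoCA (Primary outcome), measured at baseline, weeks 4 and 8, end of treatment, and months 4 and 6 after the intervention (Outcome measurements).

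**The concern.** With a sham arm, the effect of acupuncture is acupuncture minus sham. Whether that effect differs by genotype is therefore a difference of two differences. The design supplies the four cells needed to estimate it, but the only group structure fixed for testing is one factor with four levels.

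A four-group test asks whether any cell differs from any other. That null is false when acupuncture works equally well in both genotypes, and also when carriers and noncarriers simply change at different rates. Each pairwise test compares two cells. Treated carriers against treated noncarriers mixes the effect with the genotype's own level, and acupuncture against sham within one genotype says nothing about the other. None of these tests has equal effect in both genotypes as its null. At stake is a report of a genotype-dependent benefit that does not exist, or a conclusion on that purpose that rests on no estimate of it.

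**Working it through.** **Inputs from the protocol article.** Four cells, 30 per cell (120 in total), 96 before the dropout allowance (24 per cell), effect size 0.4, test level 0.05, power 0.9. The effect size is taken to be Cohen's f, which is an assumption. The article gives no SD for MoCA and no expected difference, so effects below are in SD units and shown as a range.

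**1. Reproduce the plan's figure.** One-way ANOVA with k = 4, df1 = 3, df2 = N − 4, noncentrality λ = N f².
- N = 96: λ = 96 × 0.16 = 15.36, power 0.912.
- N = 92: λ = 92 × 0.16 = 14.72, power 0.898.

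The smallest balanced total is 96, as stated. The trial is sized on a 3-df omnibus test.

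**2. Compare the nulls.** Write the cell means as CA, CS (carriers, acupuncture and sham) and NA, NS (noncarriers).
- Stated purpose: (CA − CS) − (NA − NS) = 0, 1 df.
- Four-group test: CA = CS = NA = NS, 3 df.

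**3. What f = 0.4 can mean.** For cell means (d, 0, d, 0), an equal effect d in both genotypes, the SD of the four means is d/2. So f = 0.4 when d = 0.8. At 24 per cell the one-way ANOVA then rejects in 91% of trials although the effects do not differ at all.

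**4. Rejection rates when the effects are equal.** Normal data, SD 1, one time point, two-sided 0.05, 5,000 trials per row. Within-genotype rank sum tests use 0.05/6 (six pairs among four groups).

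| True state | Per cell | Kruskal–Wallis | Two within-genotype tests disagree | 1-df interaction |
|---|---|---|---|---|
| No differences | 30 | 4.7% | 1.5% | 5.4% |
| Equal 0.5 SD effect | 30 | 58.3% | 32.0% | 4.5% |
| Equal 0.8 SD effect | 30 | 95.9% | 47.9% | 5.6% |
| Genotype only, 0.5 SD | 30 | 57.0% | 1.4% | 5.1% |
| Genotype only, 0.8 SD | 30 | 95.4% | 1.5% | 4.7% |
| Equal 0.5 SD effect | 24 | 47.9% | 25.6% | 4.7% |
| Equal 0.8 SD effect | 24 | 89.3% | 48.8% | 4.0% |

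A separate run of 20,000 trials at 24 per cell gave 47.0% and 89.3% for Kruskal–Wallis under the equal effects, and 5.1% and 4.8% for the interaction. With t contrasts in place of rank sum tests, the within-genotype tests disagreed in 28.3% and 48.2%.

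**5. Precision of the interaction.** Its standard error is √(4/n) SD: 0.365 at n = 30 and 0.408 at n = 24. A difference in effects Δ gives f = Δ/4, so Δ = 0.8 gives f = 0.2.
- N = 120: λ = 120 × 0.04 = 4.8, power 58%.
- N = 96: λ = 96 × 0.04 = 3.84, power 49%.

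**6. Repeated-measures ANOVA.** If group enters with four levels, group × time has 3 df for each time contrast (3 × 5 = 15 over the six occasions). Its null is that all four groups change alike, which again is not equal effect in both genotypes. If arm and ε4 status enter separately, the model contains the right term. The article does not say which. This model was not simulated.

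**The case against.** - **Repeated-measures ANOVA is the method that fits MoCA over time.** The Sample size section need not fix the analysis model, and two genotype groups each randomised to two arms fit a two-factor model naturally. This stands in part. A reader might infer that the question has no valid test; the article does not support that, because the named ANOVA could carry the interaction. What remains is that no such term is stated and the only group structure given is the four-level one.
- **An article condenses, and model terms may be in a fuller document.** Silence alone would be no finding. Here the article positively states a one-factor structure that does not match the purpose in its Discussion.
- **Other aims are stated.** The Abstract speaks of improvement in patients with and without ε4, and the Discussion also gives the link between acupoints and gut microbiota as a purpose. The Discussion calls the study a pilot. This stands: the interaction is one purpose among several, and four-group and within-genotype tests can serve others.
- **Nowhere is an omnibus rejection, or significance in one genotype only, said to count as a genotype difference.** This stands. The percentages apply only if the results are read that way.
- **A level difference between genotypes may not matter.** A stable baseline gap cancels in change scores. The genotype-only rows apply only if the genotypes differ in change.
- **A reader might infer that the four-group test generally loses about 20 points of power.** With effects of +0.4 and −0.4 SD and main effects that cancel, Kruskal–Wallis rejects in 39% against 58% for the interaction. With the same effects and equal sham means it rejects in about 70%, and with a 0.8 SD effect in one genotype only in 88%, both against about 58%. So there is no general loss, although those rejections do not isolate the interaction.

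**Conclusion.** The point holds as a mismatch between one stated purpose and the group structure fixed for testing. As specified, none of the named tests has equal effect in both genotypes as its null. The repeated-measures ANOVA would have such a test only if arm and genotype entered as separate factors with their interaction.

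The risk is conditional on how results are read, but large if they are misread: at 30 per cell, 58% to 96% for the omnibus test and about 32% to 48% for discordant significance, against about 5% for the interaction. These figures assume normal data, a single time point, equal effects of 0.5 to 0.8 SD and Bonferroni adjustment over six pairs. The direction does not depend on those values, because any nonzero equal effect makes the four-group null false.

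**What to change.** In the Data analysis section, state for MoCA a model with arm (acupuncture, sham) and ε4 status (carrier, noncarrier) as two separate factors, their interaction, and adjustment for baseline MoCA. In the repeated-measures model, include arm × ε4 × time and name the visit, or the average over visits, at which the 1-df arm × ε4 contrast is read. If baseline MoCA is the covariate, only later visits are responses.

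Base any claim that acupuncture works differently by genotype solely on that 1-df estimate and its 95% CI. Report the effect within each genotype with its CI as descriptive, and say that significance in one genotype and not the other is no evidence of a difference. Kruskal–Wallis and pairwise tests may stay for other questions.

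The cost is wording only: arm, genotype and baseline MoCA are already collected. The downside is imprecision, with about 58% power for a 0.8 SD difference in effects at 30 per cell and about 49% at 24, so the genotype claim will be more cautious.
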